**Methods:**

The Joint PRehabilitation with Exercise and Protein (Joint PREP) study is a feasibility study for a multicentre, two-arm, parallel group, pragmatic, RCT to evaluate the clinical and cost-effectiveness of prehabilitation for frail patients undergoing total hip or knee replacement. Sixty people who are ≥ 65 years of age, frail according to the self-reported Groningen Frailty Indicator, and scheduled to undergo total hip or knee replacement at 2–3 hospitals in England and Wales will be recruited and randomly allocated on a 1:1 ratio to the intervention or usual care group. The usual care group will receive the standard care at their hospital. The intervention group will be given a daily protein supplement and will be asked to follow a home-based, tailored daily exercise programme for 12 weeks before their operation, in addition to usual care. Participants will be supported through six follow-up calls from a physiotherapist during the 12-week intervention period. Study questionnaires will be administered at baseline and 12 weeks after randomisation. Embedded qualitative research with patients will explore their experiences of participating, reasons for nonparticipation, and/or reasons for withdrawal or treatment discontinuation. Primary feasibility outcomes will be eligibility and recruitment rates, adherence to the intervention, and acceptability of the trial and the intervention.

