#### Progression criteria for a full-scale RCT

The key feasibility issues will be considered on a red (stop), amber (amend), and green (proceed) traffic light system. The feasibility of a full trial will be determined by overall recruitment, retention, and adherence rates. Recruitment will be considered achievable if the rate observed is > 23% (lower limit of the 95% confidence interval for a 30% recruitment rate based on 200 screened). Similar criteria will be applied for retention: i.e. > 70%, for an 80% retention rate based on 60 participants, for adherence: > 37%, and for a 50% adherence rate based on 60 participants. If all three elements fail to reach the threshold (i.e. recruitment is ≤ 23%, retention is ≤ 69%, and adherence is ≤ 37%), a RCT will not be considered feasible. If one or two elements fail to reach the threshold, we will consider how the trial can be modified to address the shortfall. Examples may include modifying recruitment processes or study documents (recruitment), providing additional support/advice (retention and adherence), or offering alternative protein-rich products/exercises (retention and adherence). If all three elements are above the threshold, the trial will be considered feasible.

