### Sample size

As this is a feasibility study, we have based our sample size on recruitment rate. If we identify 200 eligible patients, we can estimate a recruitment rate of 30% (i.e. 60 participants) to within a 95% confidence interval of ± 6.35%.

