### Statistical analysis

This study is not powered to look at differences in outcomes between the intervention and usual care group. Data on recruitment, retention, and adherence will be reported using frequencies and proportions with 95% confidence intervals. Sample characteristics and outcome data will be summarised by means and standard deviations, medians and interquartile ranges, or frequencies and proportions as appropriate. Preoperative WOMAC scores will be summarised by group and compared descriptively to estimate the efficacy potential of the intervention.

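### The recruitment 'proceed' threshold of 23% is not the confidence limit it is said to be (23.65%), and passing it shows only that the rate is not clearly below the planning rate

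*Protocol article*

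**What the plan says.** All of this is in the protocol article.

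- **Progression criteria for a full-scale RCT**, recruitment: "Recruitment will be considered achievable if the rate observed is > 23% (lower limit of the 95% confidence interval for a 30% recruitment rate" and the denominator is given as "based on 200 screened". The fail rule uses the same figure, at or below 23%.
- The same section applies the approach to retention (bar 70%, "for an 80% retention rate based on 60 participants") and to adherence (bar 37%, "for a 50% adherence rate based on 60 participants").
- The green rule is: "If all three elements are above the threshold, the trial will be considered feasible". One or two elements short leads to modification. All three short means not feasible.
- **Sample size**: "we can estimate a recruitment rate of 30% (i.e. 60 participants) to within a 95% confidence interval of ± 6.35"%, with 200 patients as the denominator.
- **Statistical analysis**: "Data on recruitment, retention, and adherence will be reported using frequencies and proportions with 95% confidence intervals". The progression rule does not use these intervals. It compares the observed rate alone with the bar.

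**The concern.** The recruitment bar is defined by a calculation, and the printed number does not match it. The Sample size section fixes the lower limit at 23.65%, whereas the decision rule uses 23%. An observed rate between the two is therefore called achievable by the number and not achievable by its definition.

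The way the bar is built also limits what a pass can mean. Each bar is the lower 95% limit around a planning rate (30%, 80%, 50%), and only the point estimate is compared with it. Clearing the bar shows that the result is not clearly below the planning rate. It does not show that the rate is at or near that value. The feasibility verdict is the study's primary outcome, so a reader could take green as support for planning the RCT on 30%, 80% and 50% when the data support something lower.

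**Working it through.** **Inputs.** Planning rates 30%, 80% and 50%; denominators 200, 60 and 60; bars 23%, 70% and 37% (Progression criteria). Half-width 6.35 points (Sample size).

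**1. Reproduce the plan's half-width.** Wald: 1.96 × √(0.30 × 0.70 / 200) = 0.0635. This matches the stated 6.35.

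**2. Lower limits around the planning rates.**

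| Element | Wald lower limit | Printed bar | Smallest passing count |
|---|---|---|---|
| Recruitment, 30% of 200 | 0.30 − 0.0635 = 23.65% | 23% | 47/200 (23.5%) |
| Retention, 80% of 60 | 0.80 − 0.1012 = 69.88% | 70% | 43/60 (71.7%) |
| Adherence, 50% of 60 | 0.50 − 0.1265 = 37.35% | 37% | 23/60 (38.3%) |

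Retention is rounded to the nearest whole number. So is adherence, with no effect, because no count out of 60 lies between 37% and 37.35%. Recruitment is cut down rather than rounded: 23.65% would round to 24%. Other interval methods do not rescue 23%, since for 60/200 the exact lower limit is 23.74% and the Wilson limit 24.07%.

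**3. The result that changes sides.** 47/200 = 23.5% is above 23% but below 23.65%. Its own 95% interval is 17.6% to 29.4% (Wald), 18.2% to 29.8% (Wilson) or 17.8% to 29.996% (exact). All three exclude 30%. The score statistic against 30% is (0.235 − 0.30) / √(0.21/200) = −2.01. The next count, 48/200 = 24.0%, is above 23.65% and has a score statistic of −1.85. Its Wilson interval is 18.6% to 30.4%, which includes 30%. Its Wald interval ends at 29.9%, so by that method it still just misses 30%.

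**4. What a pass means.** Exact binomial chance that recruitment passes, P(X ≥ k) with n = 200:

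| True rate | k = 47 (printed bar) | k = 48 (corrected bar) |
|---|---|---|
| 20% | 13% | 9% |
| 23% | 46% | 40% |
| 23.65% | 55% | 48% |
| 25% | 71% | 65% |
| 27% | 89% | 85% |
| 30% | 98% | 98% |

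The other elements, at the stated n = 60:

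- Retention (k = 43): 45% pass at a true 70%, 78% at 75%, 96% at 80%.
- Adherence (k = 23): 46% pass at a true 37%, 65% at 40%, 97% at 50%.

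Only about 30 participants receive the intervention ("randomly allocated on a 1:1 ratio to the intervention or usual care group"). With n = 30 (k = 12), adherence passes 43% of the time at a true 37% and 57% at 40%.

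**5. Joint verdict, assuming the elements are independent and adherence n = 60.** All three truly at the planning rates: 0.983 × 0.957 × 0.974 = 92% all-green. All three moderately short (25%, 75%, 45%): 0.713 × 0.775 × 0.879 = 49%, or 42% with adherence n = 30.

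**The case against.** The strongest reply is that this is a feasibility study sized for precision and the protocol states no hypothesis test. Nothing in it says that rates below 30%, 80% or 50% are inadequate, so 23%, 70% and 37% can be read as the acceptable minima. On that reading 23% is a convenient whole number, and the gap is one participant in 200. The rates will be reported with intervals, and interviews and staff discussions also inform the next step.

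Much of this stands, and it rules out several stronger readings that a reader might infer:

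- *The rule usually misses a real shortfall.* This holds per element only for shortfalls well inside the half-width. Larger ones are mostly caught: recruitment truly at 20% fails 87% of the time, retention at 65% fails 83%, and adherence at 30% fails 90% (84% with n = 30). Green also needs all three elements to pass.
- *The bar loosens with less data.* The printed bars are fixed numbers. For adherence, the lower limit for 50% with n = 30 would be 32.1%, so 37% is the stricter bar.
- *A green result can contradict all three planning rates at once.* Pooling the minimum passes 47/200, 43/60 and 23/60 describes data that cannot occur, because 47 recruits cannot supply a denominator of 60. Taken singly, the smallest passing retention and adherence results have Wilson intervals that include their planning rates (59.2% to 81.5%; 27.1% to 51.0%).
- *The RCT would be launched on unsupported rates.* The protocol does not say that it would be planned on 30% and 80% whatever is observed.

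The reply does not dispose of the recruitment threshold. The protocol presents 23% as a specific confidence limit, not as a freely chosen minimum, and its own arithmetic gives a different number.

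**Conclusion.** The recruitment threshold is wrong by its own definition: 23% is printed where the stated calculation gives 23.65%. At 200 patients this affects one outcome, 47/200, which changes sides, and it moves the pass chance at a true 25% from 71% to 65%. That is small, but it sits in the rule that gives the study's main verdict.

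Separately, a pass should not be read as evidence that a rate is adequate. At the printed floors each element passes 45% to 46% of the time (43% for adherence with n = 30). This follows from comparing a point estimate with a bar, and correcting the recruitment figure does not remove it: at a true 23.65% the corrected bar is still passed 48% of the time. It calls for a plain statement, not a different rule.

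The figures assume simple binomial sampling and the protocol's denominators. The joint figures also assume independence between elements.

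**What to change.** 1. In the progression criteria, replace 23% with 23.65% in both places: pass if the observed recruitment rate is above 23.65% (at least 48 of 200), fail if it is at or below 23.65%. This agrees with the Sample size section. It is a wording change only, and a study truly at 30% still passes 98% of the time.
2. Add a sentence saying that clearing a threshold means only that the observed rate is not clearly below the planning rate, that the reported 95% intervals will be read beside the verdict, and that the full RCT will be planned on the observed rates. No new data are needed.

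Optional: green could be moved up to 30%, 80% and 50%. Passing at a true 25% recruitment would fall to about 6%. The price is high, because a study truly on its planning rates would be all-green only 0.527 × 0.576 × 0.551 = 17% of the time (independence, adherence n = 60), against 92% now. Amber and red would also have to be redefined, since they now depend on how many elements fail. The investigators may reasonably decline this.

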## Background

Total hip replacement (THR) and total knee replacement (TKR) are two of the most common elective surgical procedures; in the UK, > 200,000 are performed annually in the National Health Service (NHS) [1, 2]. Joint replacement is performed to provide relief from chronic pain and improve functional ability and is successful for many patients [3]. However, there are a proportion of patients who experience adverse post-operative outcomes, including surgical and medical complications, mortality, chronic postsurgical pain, and long-term functional limitations [4–7]. Research has found that although people with frailty often experience improvements in function and pain with joint replacement, they are particularly susceptible to the risks associated with surgery [8–12]. Frailty is a syndrome, whereby decline in physiological reserve and function confers increased vulnerability to physiological stressors such as surgery.

The prevalence of frailty in community-based adults aged ≥ 50 years in England is estimated to be 8% [13]. Studies from North America show that one-third to one-half of those waiting for a joint replacement are frail [10, 14]. In the UK, the average age of those undergoing THR or TKR is approximately 70 years [1], suggesting that many operations are carried out in frail individuals. Following joint replacement, frailty has been associated with increased mortality, length of hospital stay, admission to intensive care, discharge to institutional care, readmissions, and poorer patient-reported outcomes [8–12]. The prevalence of frailty among patients undergoing joint replacement in the NHS is likely to continue to grow due to the ageing population and increased waiting times for surgery [15].

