#### Screening and recruitment

NHS patients on waiting lists for a THR or TKR who are aged ≥ 65 years and within an appropriate window prior to their anticipated date of surgery (i.e. as close to 12 weeks prior to surgery as possible) will be identified by the clinical care team and sent a study information pack and screening questionnaire. The screening questionnaire includes demographic questions, the Groningen Frailty Indicator [21], the self-reported version of the Clinical Frailty Scale [22], and questions about ability to participate in exercise, consume extra protein, and participate in other studies. Interested patients are asked to complete and return the screening questionnaire and consent form in a pre-paid self-addressed envelope. One reminder pack will be sent if no response is received within 1 to 2 weeks, followed by a telephone call to ask if they would like any additional support to participate, such as completing the questionnaire over the telephone. Patients who return a screening questionnaire and consent form and meet the eligibility criteria will then be telephoned by the local research team to confirm that they fully understand what participation involves, answer any questions, and explain what will happen during the study. Participants will then be sent a baseline questionnaire to complete. All patients meeting the eligibility criteria will be invited to consider participation in a telephone/online semi-structured interview.

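### The 23% recruitment bar is set on 200 screened patients, but the sample size sets the same calculation on 200 eligible patients, so the same data can pass or fail

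*Protocol article*

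**What the plan says.** Two sections of the Protocol article describe what is plainly one calculation.

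- **Progression criteria for a full-scale RCT.** "Recruitment will be considered achievable if the rate observed is" above 23%, and this figure is explained as the "lower limit of the 95% confidence interval for a 30% recruitment rate based on 200 screened".
- **Sample size.** "If we identify 200 eligible patients, we can estimate a recruitment rate of 30% (i.e. 60 participants"), and this is "to within a 95% confidence interval of" ± 6.35%.

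Three other sections bear on whether screened and eligible could be the same group.

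- **Eligibility criteria.** A Groningen Frailty Indicator score of at least 4 is required, and contraindications to the study treatments exclude.
- **Screening and recruitment.** Packs go to patients picked by waiting list, age and surgery window. Frailty and ability to take part are asked about in the screening questionnaire: "Interested patients are asked to complete and return the screening questionnaire and consent form".
- **Primary feasibility outcomes.** The eligibility rate is listed as an uncertainty alongside the recruitment rate. Eligible, approached and consented patients are all to be counted, but none is named as the denominator of the recruitment rate.

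**The concern.** Recruitment is the only parameter the study is sized on, a primary feasibility outcome, and one of the three elements of the traffic-light decision. Its bar is a fixed percentage, so it has meaning only with a fixed denominator. The article gives two, and by its own design they are different groups: a patient is screened before frailty and ability to take part are known, and is eligible only afterwards.

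At stake is the formal conclusion on recruitment. Recruitment that goes exactly to the sample size plan can be reported as meeting the bar or as missing it, depending on which sentence is followed. With both sentences in print, the choice could be made after the counts are known.

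**Working it through.** **Inputs**

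| Quantity | Value | Source |
|---|---|---|
| Expected recruitment rate, p | 0.30 | Sample size; Progression criteria |
| Number, n | 200 (eligible in one place, screened in the other) | Sample size; Progression criteria |
| Recruits | 60 | Sample size |
| Stated half-width | 6.35 points, 95% | Sample size |
| Bar | above 23% passes, 23% or below fails | Progression criteria |
| Eligible share of those screened, e | not given for these sites | varied below |
| Frailty share, illustration only | 1/3 to 1/2, North American studies | Background |

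**Step 1: reproduce the plan's figure.** Wald half-width = 1.96 × √(p(1 − p)/n) = 1.96 × √(0.30 × 0.70/200) = 0.0635. This matches the stated ± 6.35%. The lower limit is 30 − 6.35 = 23.65%, and the bar is that figure rounded down to 23%. Other intervals barely move it: the Wilson lower limit is 24.07% and the Clopper-Pearson lower limit 23.74%. The word screened or eligible does not enter the formula, so the arithmetic is correct under either label and cannot settle which is meant.

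**Step 2: apply both denominators to the same data.** Take the planned result, 60 recruits from 200 eligible patients.

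- Eligible denominator: 60/200 = 30%, a pass.
- Screened denominator: 200 eligible patients come from 200/e screened, so the rate is 60/(200/e) = 0.30 × e.

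| e | Screened (200/e) | 60/screened | Against 23% |
|---|---|---|---|
| 0.80 | 250 | 24.0% | pass |
| 0.75 | 267 | 22.5% | fail |
| 0.50 | 400 | 15.0% | fail |
| 1/3 | 600 | 10.0% | fail |

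**Step 3: break-even.** 0.30 × e = 0.23 gives e = 0.23/0.30 = 76.7%, or 60/0.23 = about 261 screened. Above that share the planned result passes on both denominators; at or below it, the two disagree.

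**Step 4: a plausible place for e, as an assumption.** The Background reports that "one-third to one-half of those waiting for a joint replacement are frail", from North American studies. If that range applied here and every frail patient were otherwise eligible, the screened-based rate would be 0.30 × 1/3 = 10% to 0.30 × 1/2 = 15%.

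**Step 5: effect on the decision.** Under the Progression criteria, one or two missed elements lead to modification and all three must fail for a stop. With retention and adherence met, the choice of denominator moves the result from green to amber. It decides between amber and stop only if both of the others have failed.

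**The case against.** The mismatch itself has no good defence: nothing in the article reconciles the two labels, and because both are stated this is not detail left to a fuller document. The case on the other side concerns how much can be built on it, and most of that case stands. A reader might infer four stronger things.

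- *On screened patients the bar is close to unreachable.* With 200 screened and one-third to one-half eligible there would be 67–100 eligible patients. Passing needs at least 47 recruits, so uptake of 47/100 = 47% to 47/67 = 70%. The Discussion cites a home-based pilot in frail patients with 70% recruitment, and this intervention is home-based. If 70% were uptake among eligible patients (the denominator of that rate is not given), the screened-based rate would be 0.70 × 1/3 = 23% to 0.70 × 1/2 = 35%, borderline to a clear pass. Moreover, screened is undefined. If it means a returned questionnaire rather than a pack sent, many of the counted patients have already consented and the bar is easier.
- *On eligible patients the bar is passed almost automatically.* Because the questionnaire and consent form are returned together, eligibility will be known mainly in people who have consented, which pushes the rate upwards. The size of this is not known. A telephone call and a completed baseline questionnaire still come before randomisation, non-responders get a reminder and a call, and the article does not say that a questionnaire returned without consent is discarded.
- *Recruitment alone decides go or no-go.* It does not; Step 5 gives the actual rule.
- *The next trial would not learn how many patients to approach.* The approached, eligible and consented counts are collected in any case. The defect lies in the threshold, not in the data.

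The frailty range is also not specific to these sites, to patients aged 65 or over, or to the Groningen cut-off. It serves as an illustration only.

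**Conclusion.** The point holds as a contradiction between two sections about the denominator of a decision threshold. With the planned 60 recruits from 200 eligible patients, recruitment passes at 30% on one denominator and fails on the other once the eligible share of those screened is below about 77%. That break-even uses only the article's own 30% and 23%. The 10–15% figure rests on two added assumptions: that the North American range applies, and that all frail patients are eligible. If 77% or more of those screened were eligible, the planned result would pass either way, so the correct statement is that the same data *can* pass or fail, not that they must. The usual consequence is green versus amber. The documents do not support going further and calling the bar unreachable on one reading or automatic on the other.

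**What to change.** Name one explicitly defined denominator for the recruitment rate and use it in both Sample size and Progression criteria, before the recruitment counts are reviewed against the bar.

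- **If eligible is meant:** change the Progression criteria to 200 eligible and keep the 23% bar. Say how eligibility is counted for patients who do not return the consent form, since it will otherwise be known mainly in those who have already consented.
- **If screened or approached is meant:** say whether that is a pack sent or a questionnaire returned. Then restate the expected rate, the number to be screened and the lower-limit bar on that denominator. The 30% and 23% should not be carried over unless 30% really is the expectation among that group.

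Either way, report the approached, returned, eligible and randomised counts, with 95% intervals for the proportions between them, from the screening and recruitment records already planned. The next trial can then be planned whichever definition is chosen.

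The cost is a wording change in two sections and, under the second option, recalculation of one bar. Neither the target of 60 nor the recruitment process has to change to remove the contradiction. Moving to an approached-based bar, or inviting questionnaires without consent, would be a design preference and is not required.

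### Retention passes above 70% but fails only at 69% or below, so 42 of 60 retained (70.0%) has no verdict

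*Protocol article*

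**What the plan says.** The Protocol article, under Progression criteria for a full-scale RCT, sets each bar from the lower confidence limit of an expected rate. For recruitment the bar is above 23%, explained as the "lower limit of the 95% confidence interval for a 30% recruitment rate based on 200 screened". The text then continues "Similar criteria will be applied for retention" and gives "i.e. > 70%, for an 80% retention rate based on 60 participants" and "for adherence: > 37%, and for a 50% adherence rate based on 60 participants".

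The same section defines failure on all three elements as "recruitment is ≤ 23%, retention is ≤ 69%, and adherence is ≤ 37" per cent. This is the only place where failing is given in numbers.

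The decision rules count elements against a single threshold. The trial is feasible if all three are above it, is reconsidered with modifications if one or two fall short, and is not feasible if all three fall short.

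**The concern.** Recruitment is > 23% to pass and ≤ 23% to fail. Adherence is > 37% to pass and ≤ 37% to fail. Both pairs cover every possible result. Retention is > 70% to pass and ≤ 69% to fail, which leaves the interval above 69% and up to and including 70% unclassified.

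The amber category does not fill this gap. It is defined by how many elements fall short, not by an intermediate band within one element.

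These rules produce the study's main output, a judgement on whether a full RCT is feasible. If retention lands in the gap, someone must decide after the data are known which of the two printed figures applies. Pre-set criteria exist to prevent that.

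**Working it through.** **Inputs** (all from the Protocol article)

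- Expected rates and denominators, from Progression criteria: recruitment 30% of 200, retention 80% of 60, adherence 50% of 60.
- Interval check, from Sample size: "we can estimate a recruitment rate of 30% (i.e. 60 participants) to within a 95% confidence interval of ± 6.35" per cent.
- Planned number randomised, from the abstract's Methods: 60.

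**Step 1. Reproduce the plan's own interval.** With the normal-approximation interval p ± 1.96·√(p(1−p)/n), recruitment has half-width 1.96 × √(0.30 × 0.70/200) = 1.96 × 0.03240 = 0.0635. This matches the stated 6.35 points, so the method is identified.

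**Step 2. Apply it to the three bars.**

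| Element | Calculation | Lower limit | Truncated | Rounded | Printed pass | Printed fail |
|---|---|---|---|---|---|---|
| Recruitment | 0.30 − 0.0635 | 23.65% | 23 | 24 | > 23 | ≤ 23 |
| Retention | 0.80 − 1.96 × √(0.80 × 0.20/60) = 0.80 − 0.1012 | 69.88% | 69 | 70 | > 70 | ≤ 69 |
| Adherence | 0.50 − 1.96 × √(0.50 × 0.50/60) = 0.50 − 0.1265 | 37.35% | 37 | 37 | > 37 | ≤ 37 |

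The retention pass mark equals the limit rounded. The fail mark equals the limit truncated, which is also the convention that gives recruitment its 23%. Both printed figures appear to come from the same 69.88%.

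**Step 3. Does the choice of interval matter?** Other lower limits for 48/60 are Wilson 68.22%, Clopper-Pearson 67.67%, Agresti-Coull 68.07%, Jeffreys 68.61% and continuity-corrected Wald 69.05%. All are below 70%, so 42/60 exceeds the limit under every method tried.

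**Step 4. Classify the counts out of 60.**

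- 41/60 = 68.33%: fail.
- 42/60 = 70.00%: not above 70%, and not 69% or below.
- 43/60 = 71.67%: pass.

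42 is the only count out of 60 in the gap. Other denominators close to 60 also have a gap count (39/56 = 69.6%, 41/59 = 69.5%, 43/62 = 69.4%), while 57, 58 and 61 have none.

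**Step 5. How likely is it?** With the number retained taken as X ~ Binomial(60, p):

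| True retention | P(X = 42) |
|---|---|
| 80% (planning value) | 2.1% |
| 75% | 7.6% |
| 70% | 11.2% |

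At p = 70%, the chance of passing is P(X ≥ 43) = 45.1% if 42 does not pass and P(X ≥ 42) = 56.3% if it does. The difference is the 11.2% chance of exactly 42.

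**Step 6. Which decisions are affected?** With 42 retained:

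- If recruitment and adherence both pass, green does not apply because retention is not above 70%. Amber does not apply on the printed numbers because no element meets a fail mark.
- If recruitment and adherence both fail, it is open whether two elements have failed (amber) or three (red).
- If exactly one of the other two fails, the outcome is amber on either reading.

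**The case against.** The best defence is that the literal text already settles green. The only pass mark printed is > 70%, and 42/60 does not exceed it, so the trial is not green and drops to amber by elimination. On this view the ≤ 69% figure matters only for red against amber, and only when recruitment and adherence have both failed. Amber is discretionary in any case, and no treatment comparison or safety decision depends on it.

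A second defence is that > 70% is a slip for ≥ 70% with rates read as whole percentages. The retention pair would then be complementary. 42/60 and 39/56 would pass, 41/59 (69.49%) would round to 69 and fail, and no gap would remain.

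A third is scale. The gap is one count, about 2% likely at the protocol's own planning value. The 11.2% and the 45% against 56% arise only when true retention sits on the boundary, where any cut-off is sensitive to one participant.

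The third point stands and limits the size of the finding. The first does not close the gap: amber, like red, requires elements that fall short, and the only numerical definition of falling short on retention is ≤ 69%. The second is plausible, but the document states no rounding rule and uses strict inequalities with one figure on both sides for the other two elements. It would also make 42/60 a pass, whereas the first defence makes it a non-pass. Two reasonable readings with opposite results show that the sentence needs correcting.

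**Conclusion.** The concern holds. The retention pass and fail marks are inconsistent as printed, and 42 of 60 retained has no defined classification, although 70.0% lies above the 69.88% limit (by 0.12 percentage points under the interval that reproduces the protocol's ± 6.35%, and by more under the alternatives tried).

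The practical reach is small: one count at the planned size, with probability 2.1% at 80% true retention, rising to 11.2% at 70%. The consequence if it occurs is an open choice between green and amber, or between amber and red, on the study's main conclusion.

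The probabilities assume a retention denominator of exactly 60 and independent participants with a common retention probability. The 69.88% is calculated here and is not printed in the protocol.

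**What to change.** State one retention cut-off and make pass and fail complements. For example, pass if retention is at least 70% (42 or more of 60) and fail if it is below 70%. This agrees with the computed limit of 69.88% and keeps 41/60 a fail. The pair > 69% and ≤ 69% gives the same classification at 60. The pair > 70% and ≤ 70% would also close the gap, but it would fail 42/60 although that result exceeds the limit the bar is based on.

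The cost is one sentence in the progression criteria, with no effect on design, sample size or data collection. The change should be made before the retention data are seen.

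### The retention pass mark (> 70%) and fail mark (≤ 69%) do not meet, so 42 of 60 retained (70.0%) falls under neither

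*Protocol article*

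**What the plan says.** All the relevant text is in the protocol article, mainly in the section on progression criteria for a full-scale RCT.

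- **Basis of the bars.** The recruitment bar of 23% is described as the "lower limit of the 95% confidence interval for a 30% recruitment rate based on 200 screened".
- **Retention pass mark.** The bar is > 70%, set on the same basis as recruitment, "for an 80% retention rate based on 60 participants".
- **Fail marks.** The stop rule lists, as percentages, "recruitment is ≤ 23%, retention is ≤ 69%, and adherence is ≤ 37".
- **Green.** "If all three elements are above the threshold, the trial will be considered feasible".
- **Amber.** "If one or two elements fail to reach the threshold, we will consider how the trial can be modified to address the shortfall".
- **Red.** All three elements fail to reach the threshold, using the fail marks above.

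The Sample size section gives the precision for recruitment: "we can estimate a recruitment rate of 30% (i.e. 60 participants) to within a 95% confidence interval of ± 6.35" percentage points.

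**The concern.** Recruitment passes above 23% and fails at or below 23%; adherence passes above 37% and fails at or below 37%. Each pair covers every possible result. The retention pair does not, because nothing is said about a rate above 69% and up to 70%. That interval contains a result that can occur at the planned sample size.

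Determining feasibility is the study's primary outcome, and retention is one of three rates that decide it. If the observed count fell in the gap, the team would have to choose a reading after seeing the data, which a pre-specified progression rule is meant to prevent.

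**Working it through.** **Inputs.** Anticipated rates and denominators are 30% of 200, 80% of 60 and 50% of 60 (progression criteria). The recruitment half-width is 6.35 points (Sample size). The retention marks are > 70% and ≤ 69% (progression criteria).

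**Step 1: identify the interval method from the plan's own figure.** The normal-approximation half-width for recruitment is 1.96·√(0.30·0.70/200) = 6.35 points, which reproduces the stated figure. The lower limit is 30 − 6.35 = 23.65%, stated as 23%.

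**Step 2: apply the same formula to the other two elements.**
- Retention: 1.96·√(0.80·0.20/60) = 1.96 × 0.05164 = 10.12 points; lower limit 80 − 10.12 = 69.88%.
- Adherence: 0.50 − 1.96·√(0.50·0.50/60) = 37.35%, stated as 37%.

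The retention limit of 69.88% becomes 70 if rounded and 69 if truncated. Those are the two figures printed, so both probably come from the same limit.

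**Step 3: test the counts out of 60.**

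| Retained | Rate | > 70%? | ≤ 69%? |
|---|---|---|---|
| 41/60 | 68.33% | no | yes (fails) |
| 42/60 | 70.00% | no | no |
| 43/60 | 71.67% | yes (passes) | no |

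Only 42 falls in the gap. It lies above the 69.88% limit but does not satisfy > 70%. It would also lie above the lower limit by other common methods (Wilson 68.22%, exact 67.67%, continuity-corrected normal 69.05%).

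**Step 4: overall result at 42/60.**

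| Recruitment and adherence | Literal wording | If 42/60 counts as failing | If 42/60 counts as passing |
|---|---|---|---|
| Both pass | neither green nor amber | amber | green |
| Exactly one fails | amber | amber | amber |
| Both fail | amber (two fail) | red | amber |

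**Step 5: how likely the count is.** Taking the number retained as binomial with n = 60, P(exactly 42) is 0.021 at true retention of 80%, 0.076 at 75% and 0.112 at 70%.

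**Step 6: other denominators.** If the number randomised is not exactly 60, other counts can fall in the gap: 41/59 = 69.49%, 43/62 = 69.35%, 44/63 = 69.84%.

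**The case against.** The strongest reply is that a workable reading exists. The stated retention criterion is > 70%, and 69% appears only in a parenthesis of the stop rule. If 69% is a slip, 42/60 simply fails, and with the other two elements passing the result is amber. Amber only leads to considering changes to the trial, so stopping is not in question there. This limits the practical consequence but does not remove the conflict. The stop and amend rules both turn on failing to reach the threshold, and the only figure attached to failing on retention is ≤ 69%. The reading also fails a count that lies above the limit from which the bar was derived.

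It is also fair to say that the figures in Step 5 are probabilities of the count, not of a changed decision. A changed decision also requires the other two elements both to pass or both to fail. The 11.2% figure assumes true retention at the boundary; at the planned 80% it is 2.1%. If observed rates were reported as whole percentages (an assumption), 41/59 and 43/62 would become 69% and fail, leaving 44/63 and 42/60 in the gap.

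A reader might infer that the recruitment bar needs correcting too, because 23.65% is stated as 23% and 47/200 = 23.5% therefore passes below the derived limit. The documents do not support treating that as the same defect. The recruitment bar is slightly lenient but unambiguous, as is adherence at 37% against 37.35%, and neither leaves anything to settle after the data are seen. Raising recruitment to 24% would overshoot the derived limit: 60/252 = 23.8% would then fail although it is above 23.65%.

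A separate analysis plan or the full protocol might give a single figure. The point does not rest on an omission, however; the article states two figures that conflict.

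**Conclusion.** The retention cut-points are inconsistent as written, and the correction is small. At the planned 60 participants exactly one count, 42, is left without a classification. It matters in two situations: with recruitment and adherence both passing, no colour applies; with both failing, the reading chosen decides between amber and red.

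A reader might infer that the progression rule as a whole is unworkable or that the stop decision is generally open. Neither follows. Every other count out of 60 is classified, and red is in play at 42/60 only when both other elements have already failed.

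The conclusion assumes a denominator of 60 and rates compared unrounded with the stated marks; 42/60 is exactly 70%, so rounding does not rescue it. The probabilities also assume independent participants with a common retention probability.

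**What to change.** State one complementary retention cut-point consistent with the derived 69.88%, and use it in the green, amber and red rules. For example: retention passes at ≥ 70% (≥ 42/60) and fails at < 70% (≤ 41/60). Giving the count for n = 60 beside the percentage removes any rounding question at the planned size.

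The cost is a small edit with one substantive effect: compared with > 70%, the lowest passing count moves from 43/60 to 42/60. Keeping > 70% and changing the fail mark to ≤ 70% would also close the gap, but it would fail a count above the derived limit. Recruitment started in December 2022, and the Regulatory approvals section sends amendments to the HRA before implementation. The change should therefore go by that route and be dated relative to any look at retention data. The recruitment and adherence bars can stay as they are.
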